### Statistical Considerations

Both primary and all secondary endpoints are displayed in Appendix C.

As this study has two primary endpoints, the Hochberg extension of the Bonferroni method for multiple comparisons will be used to test for statistical significance with an overall type I error rate less than or equal to 0.05 [16]. The statistical comparisons of the treatment arms with respect to the primary and secondary endpoints are performed using the independent-samples T-test, or Fisher's exact probability test in case of binary endpoints. All p-values are 2-sided. For clinical outcomes such as the incidence of major adverse cardiac events, Kaplan-Meier curves displaying the pattern of events over the four-month and one-year follow-up period are constructed. Statistical significance and 95-% confidence intervals are calculated using Cox' proportional hazards model.

The trial is powered to detect differences between the two groups in cMRI assessed LVEF and LVEDV at four months after STEMI. With 2 × 150 randomized patients, this trial has an 80% power to detect absolute differences of 4% in LVEF and 15 mL in LVEDV in favor of PCI of the CTO with a one-sided alpha of 5%. For this calculation we have assumed that PCI of a CTO is successful in 80% of cases. The mean global ejection fraction in patients with an untreated CTO is assumed to be 36% against 40% in patients with successful CTO treatment with a common standard deviation of 12%. Consequently, the expected global ejection fraction is 40% (0.8 × 41% + 0.2 × 36%) in patients randomized to CTO treatment against 36% in patients randomized to standard medical treatment. The calculation for the second primary endpoint is based on the assumption of a net mean LVEDV of 185 ml for patients randomized to CTO treatment and of 200 ml for patients randomized to standard medical treatment. The standard deviation for LVEDV was assumed to be 45 ml. Patients who have deceased before primary endpoint measurement will be attributed the lowest LVEF and the largest LVEDV measured in the whole study cohort. The primary endpoint will be analyzed on an intention-to-treat basis.

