### PCI of a CTO: higher risk of restenosis

Percutaneous recanalization of a CTO amenable to PCI treatment can be performed with a success rate of 70-80%, but is associated with a higher rate of restenosis compared to PCI of non-occluded vessels. Although coronary stenting has been shown to be superior to conventional balloon angioplasty, restenosis rates remain relatively high. When compared to bare metal stents, drug eluting stents (DES) are effective in decreasing the need for repeat intervention in successfully treated CTO patients.[27] However, there have been concerns about long-term delay of arterial healing as a consequence of both Sirolimus eluting stent (SES) and Paclitaxel eluting stent (PES) placement and the associated risk of late stent thrombosis. Both preclinical and clinical data for a second-generation DES, the EES, are encouraging in terms of arterial healing and low restenosis rates. The EES showed superior endothelialization compared with the PES, SES and Zotarolimus-eluting stent at 14 days after stent implantation.[28] This suggests a superior safety profile for the EES, as shown in the one-year results of the SPIRIT IV trial, randomizing 3687 patients in a 2:1 fashion to either the EES or the PES for treatment of patients with de novo coronary artery disease with a maximum of 3 lesions. The SPIRIT IV investigators reported a 0.29% ARC definite or probable stent thrombosis rate in the EES arm, as compared to 1.1% in the PES arm (p = 0.003). Furthermore, the EES performed superior over the PES regarding ischemia-driven target lesion revascularization, (3.9% vs 6.6%, p = 0.0008).[29] Although extensively studied in relatively low-risk lesions, currently data regarding the performance of the EES in CTO's are lacking.

To conclude, no clinical trial to date has investigated the effect of percutaneous recanalization of CTO's on clinical endpoints in any setting. The high case-fatality rates and inferior recovery of LV function after STEMI of patients with a CTO in a non-IRA provide the rationale for the current trial. The ongoing EXPLORE trial is the first randomized clinical trial powered to investigate clinical outcome after percutaneous treatment of a CTO. The Explore trial will determine whether recanalization of a CTO within one week after primary PCI for STEMI results in a better preserved residual left ventricular ejection fraction and reduced end-diastolic volume.

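### The stated 80% power does not follow from its own inputs (they give about 89% per endpoint), and it is computed for a one-sided, unadjusted test that the trial will not run

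*Protocol article*

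**What the plan says.** All the statistical statements stand in the protocol article, Statistical Considerations.

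- **Analysis.** For LVEF and LVEDV, "the Hochberg extension of the Bonferroni method for multiple comparisons will be used to test for statistical significance". The level for this adjustment is set as follows: "with an overall type I error rate less than or equal to 0.05". The arms are compared by the independent-samples t-test, and "All p-values are 2-sided".
- **Power.** The claim opens "With 2 × 150 randomized patients, this trial has an 80% power". Its targets are a 4-point LVEF difference and, in the article's words, "15 mL in LVEDV in favor of PCI of the CTO with a one-sided alpha of 5" per cent. The assumed SDs are 12 points for LVEF and 45 mL for LVEDV. No alpha split, endpoint correlation or attrition allowance is mentioned, and it is not said whether the 80% applies to each endpoint or to both jointly.
- **LVEF assumption.** Mean LVEF after successful CTO treatment is given as 40%, but the formula that follows uses 41% to reach an arm mean of 40%.

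Elsewhere, the Background and the Discussion (PCI of a CTO: higher risk of restenosis) call the trial "the first randomized clinical trial powered to investigate clinical outcome after percutaneous treatment of a CTO". The Discussion paragraph of the Abstract lists better clinical outcome among the results the trial is powered to examine.

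**The concern.** A power statement should describe the test that will decide the trial, and its figure should follow from its inputs. This one does neither.

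A one-sided 5% test has the same critical value in the favourable direction as a two-sided 10% test. That is twice the planned overall level, and four times the 0.025 that Hochberg applies to the smaller p-value when the larger one exceeds 0.05. A reader therefore cannot take the 80% as the chance that the planned analysis succeeds, and cannot tell whether it means each endpoint or both.

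The descriptions of the trial as powered for clinical outcome go beyond the only power calculation shown, which covers two imaging measures.

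**Working it through.** **Inputs (Statistical Considerations).** n = 150 per arm; LVEF difference 4, SD 12; LVEDV difference 200 − 185 = 15 mL, SD 45; one-sided alpha 0.05; stated power 80%.

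**Step 1: standardized effects.** 4/12 = 15/45 = 0.333, so each result below applies to either endpoint.

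**Step 2: the plan's own figure.** The expected test statistic is 0.333 × √(150/2) = 2.887. By the normal approximation, power at one-sided 0.05 is Φ(2.887 − 1.645) = Φ(1.242) = 89.3%. The noncentral t with 298 degrees of freedom gives 89.2%. The stated 80% is not reproduced.

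**Step 3: other levels at 150 per arm.**

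| Test, per endpoint | Power (normal) | Power (t) | n per arm for 80% (normal / t) |
|---|---|---|---|
| One-sided 0.05 | 89.3% | 89.2% | 112 / 112 |
| Two-sided 0.05 | 82.3% | 82.1% | 142 / 143 |
| Two-sided 0.025 | 74.1% | 73.7% | 172 / 173 |

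**Step 4: readings that would rescue 80% at one-sided 5%.**

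- Joint power on both endpoints: 0.893² = 79.7% if they are independent, 81.0% at correlation 0.3 and 82.2% at 0.5.
- About 25% not evaluable: 1 − 112/150 = 25.3%, and 112 per arm gives 80%.

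The text states neither, and both remain one-sided.

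**Step 5: the planned test.** With two endpoints, Hochberg rejects both if the larger p-value is at most 0.05. Otherwise it rejects only the endpoint with the smaller p-value, if that is at most 0.025. This was simulated with 1,000,000 bivariate normal draws per setting, two-sided p-values, 150 measured per arm and correlation 0 to 0.9. The correlation is an assumption; the article gives none.

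| Quantity | Power |
|---|---|
| Each endpoint, both effects real | 80.9% falling to 79.8% |
| At least one endpoint, both effects real | 94.0% falling to 82.0% |
| Both endpoints, both effects real | 67.8% rising to 77.7% |
| One endpoint, only that effect real | about 74% |

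**Step 6: the LVEF inputs.**

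- With 41%: 0.8 × 41 + 0.2 × 36 = 40.0, a difference of 4.0.
- With 40%: 0.8 × 40 + 0.2 × 36 = 39.2, a difference of 3.2 and a standardized effect of 0.267.

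With the smaller difference, LVEF power is 74.7% at one-sided 0.05 and 63.7% at two-sided 0.05 (normal approximation). Under two-sided Hochberg, with the LVEDV effect kept at 15 mL, it is about 62–63%.

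**Step 7: missing scans (assumption).** With 10% unmeasured (135 per arm), power at two-sided 0.05 is 77.9% (t). With 20% unmeasured (120 per arm), it is about 73% at two-sided 0.05 and 63% at two-sided 0.025.

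**The case against.** The strongest reply is that the decision rule is not in doubt. The analysis paragraph fixes two-sided p-values and Hochberg at an overall 0.05, and the one-sided alpha appears only in the sample-size sentence. This stands. A reader might infer that success could be declared at an effective two-sided 10% level, but nothing in the article provides for that.

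Second, the design assumes effects on both endpoints. On the printed 4-point and 15 mL differences, the planned test then has about 80–81% power per endpoint. This also stands: the printed number is close to the right one under those conditions, but by coincidence and not from its stated basis.

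Third, the 80% may be a joint figure or may include an attrition allowance kept in the full protocol. Either could explain the number, so the origin of the discrepancy is uncertain. Neither is stated, and neither resolves the conflict with two-sided testing.

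Fourth, loss from missing scans is partly handled: SPECT or echocardiography is permitted if cMRI becomes contraindicated (Follow-up), and deaths are assigned values (Statistical Considerations). The attrition figures in the working are therefore illustrative only.

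Finally, the clinical-outcome wording lies outside the statistical section, which names only LVEF and LVEDV. That limits the harm but leaves the contradiction.

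**Conclusion.** The point holds as two separate faults in the power statement. The stated inputs give about 89% per endpoint, not 80%, and the one-sided, unadjusted basis is not the planned test. The first is not a consequence of the second: a more liberal alpha raises power, so it cannot explain a printed figure that is too low.

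A reader might infer that the trial is badly underpowered for its primary analysis. The documents do not support this in general. The shortfall is conditional: about 74% if only one effect is real, and 68–78% if both endpoints must be won, which the article does not set as the criterion. These figures assume 300 measured patients, a 4-point LVEF difference and correlation 0 to 0.9. The larger exposure is the unreconciled LVEF assumption, since 40% after successful treatment would bring LVEF power to about 62–63%.

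The claim of power for clinical outcome contradicts Statistical Considerations. Its size cannot be given, because the article states no event rates.

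**What to change.** 1. Reconcile the 40% and 41% LVEF figures for successful CTO treatment, and state the resulting arm difference.
2. Delete the one-sided alpha. State power for the two-sided Hochberg analysis at overall 0.05, and say whether it is per endpoint, for at least one or for both. If the 4-point difference is confirmed: about 80–81% per endpoint if both effects hold, about 74% if only one holds and 68–78% for both, with all 300 measured and correlation 0 to 0.9 assumed. If the difference is 3.2 points, recompute all of these; LVEF power is then about 62–63%.
3. State any attrition allowance behind the 300.
4. Remove the claim of power for clinical outcome from the Background and Discussion, and remove clinical outcome from the powered claim in the Abstract.

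These are changes of wording. The analysis rule does not change, and correcting the statement needs no extra patients. The cost is a less favourable power statement, markedly so for LVEF if 3.2 points is the intended difference.

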### Study Organization and Monitoring

An executive committee will supervise the EXPLORE trial, while a study coordination committee will coordinate the trial and perform QCA analysis. The steering committee is responsible for design and conduct of the study. An independent data and safety monitoring board watches over the ethics of conducting the study in accordance with the Declaration of Helsinki, monitors the patient safety, and reviews safety issues as the study progresses. All major adverse cardiac events will be adjudicated by a Critical Events Committee. The specific role and information regarding each of the committees appear in appendix D.

## Discussion

### Prognosis after primary PCI

After primary PCI for acute STEMI, patients with MVD have a worse clinical outcome when compared to patients with SVD.[1,2,6,17] Previous randomized studies investigating multivessel PCI during the primary procedure or shortly thereafter have been hampered by small patient numbers and have failed to show clinical benefit of additional revascularization after primary PCI.[18,19] Furthermore, a number of observational studies investigating the value of additional revascularization after primary PCI have reported inconclusive results.[3-5,20-22]

Recently, we reported that patients with a CTO in a non-IRA are the subgroup of MVD patients who are truly at risk after primary PCI for STEMI.[6,8] A CTO in a non-IRA was a strong and independent predictor of 30-day, 1-year, and 5-year mortality whereas MVD without a CTO was only a weak predictor of 30-day mortality, and not an independent predictor of 1-year, and 5-year mortality. We reported similar results in a cohort consisting exclusively of STEMI patients with cardiogenic shock.[9] Furthermore, a CTO in a non-IRA was associated with reduced LVEF during the index hospitalization and a further reduction in LVEF within the first year thereafter.[6] Therefore, rather than a significant diseased concomitant coronary artery, a CTO in a non-IRA is a target for additional revascularization after primary PCI.

These findings drive the rationale behind the EXPLORE trial. Recanalization of a CTO in a non-IRA shortly after primary PCI may improve regional myocardial function and promote infarct healing at the border zones. These effects may attenuate the remodeling process, which may lead to a better preserved residual global LV function, decreased LVEDV, and improved survival. This trial will be the first to prospectively determine the effect of PCI of a CTO in a non-IRA in the early recovery phase after successful primary PCI for STEMI on LV performance.

### LV function after elective PCI of a CTO

LVEF and LVEDV are major prognostic determinants in patients with coronary artery disease. It is suggested that opening of CTO's in an elective setting can be of benefit by restoring blood flow to hibernating myocardium and thus improving LV function. Improvement of LV function and a reduction of both end-diastolic and end-systolic volume after recanalization of a CTO has been demonstrated in several studies, provided long-term patency could be achieved.[23-26]

### PCI of a CTO: higher risk of restenosis

Percutaneous recanalization of a CTO amenable to PCI treatment can be performed with a success rate of 70-80%, but is associated with a higher rate of restenosis compared to PCI of non-occluded vessels. Although coronary stenting has been shown to be superior to conventional balloon angioplasty, restenosis rates remain relatively high. When compared to bare metal stents, drug eluting stents (DES) are effective in decreasing the need for repeat intervention in successfully treated CTO patients.[27] However, there have been concerns about long-term delay of arterial healing as a consequence of both Sirolimus eluting stent (SES) and Paclitaxel eluting stent (PES) placement and the associated risk of late stent thrombosis. Both preclinical and clinical data for a second-generation DES, the EES, are encouraging in terms of arterial healing and low restenosis rates. The EES showed superior endothelialization compared with the PES, SES and Zotarolimus-eluting stent at 14 days after stent implantation.[28] This suggests a superior safety profile for the EES, as shown in the one-year results of the SPIRIT IV trial, randomizing 3687 patients in a 2:1 fashion to either the EES or the PES for treatment of patients with de novo coronary artery disease with a maximum of 3 lesions. The SPIRIT IV investigators reported a 0.29% ARC definite or probable stent thrombosis rate in the EES arm, as compared to 1.1% in the PES arm (p = 0.003). Furthermore, the EES performed superior over the PES regarding ischemia-driven target lesion revascularization, (3.9% vs 6.6%, p = 0.0008).[29] Although extensively studied in relatively low-risk lesions, currently data regarding the performance of the EES in CTO's are lacking.

To conclude, no clinical trial to date has investigated the effect of percutaneous recanalization of CTO's on clinical endpoints in any setting. The high case-fatality rates and inferior recovery of LV function after STEMI of patients with a CTO in a non-IRA provide the rationale for the current trial. The ongoing EXPLORE trial is the first randomized clinical trial powered to investigate clinical outcome after percutaneous treatment of a CTO. The Explore trial will determine whether recanalization of a CTO within one week after primary PCI for STEMI results in a better preserved residual left ventricular ejection fraction and reduced end-diastolic volume.

## Appendix A

### Inclusion criteria EXPLORE trial

Patients are eligible for inclusion if all of the inclusion criteria are met:

- Successful primary percutaneous coronary intervention^1 ^for acute ST elevation myocardial infarction^2^

And

- Presence of at least one chronic total occlusion located in a non-infarct related coronary artery, defined as a 100% luminal narrowing without antegrade flow or with antegrade or retrograde filling through collateral vessels

And

- Reference diameter of ≥2.5 millimeters

And

- Amenable to treatment by percutaneous coronary intervention

1 Residual stenosis of the culprit lesion < 30% and Thrombolysis In Myocardial Infarction flow ≥ 2.

2 definition according to Alpert et al. Myocardial infarction redefined - a consensus document of The joint ESC/ACC committee for the redefinition of myocardial infarction [30].

## Appendix B

### Exclusion criteria EXPLORE trial

Age > 80 years

Persistent or permanent atrial fibrillation

Known renal insufficiency (serum creatinin > 265 μmol/L or > 3.5 mg/L)

Persistent hemodynamic instability^1 ^lasting up to 48 hours after primary PCI

Cardiac events^2 ^between primary PCI and randomization

Significant left main stenosis (diameter stenosis ≥ 50%)

Severe coronary artery disease, not amenable for PCI but suitable for coronary artery bypass grafting

Severe valvular heart disease requiring cardiac surgery within four months

Clinically driven indication for implantable cardioverter defibrillator within four months

Inability to schedule the index procedure within seven days after primary PCI

Contraindication for cMRI (i.e. pacemaker, cerebrovascular clips, or claustrophobia)

Serious known concomitant disease with a life expectancy of less than one year

Circumstances that prevent follow-up

Previous participation in this trial or any other trial within the previous 30 days

1 Defined as pre-shock (heart rate > 100/min, and/or systolic blood pressure < 100 mm Hg) or shock

2 Defined as extended myocardial infarction, acute stent thrombosis, or late (> 48 hours after primary PCI) and life threatening ventricular arrythmias

PCI = Percutanous Coronary Intervention, cMRI = cardiovascular Magnetic Resonance Imaging

## Appendix C

### EXPLORE trial endpoints

#### Primary Endpoints

Measured by cardiovascular magnetic resonance imaging at 4 months:

- Left ventricular ejection fraction

- Left ventricular end-diastolic volume

### Secondary Endpoints

#### Safety Endpoints

Major Adverse Cardiac Events, defined as cardiac death, myocardial infarction or any repeat coronary

intervention* at 30 days, 4 months, and 1, 2, 3, 4, and 5 years

Stent thrombosis, classified as definite, probable or possible

#### Other Secondary Endpoints

Measured by cardiac magnetic resonance imaging at 4 months:

- Left ventricular end-systolic volume - Left ventricular segmental wall thickening

- Left ventricular mass - Infarct size (by late contrast enhancement)

N Terminal - pro Brain Natriuretic Peptide (at 4 months and 1 year, relative to baseline)

Heart rate-adjusted QT (QTc) duration measured by resting electrocardiography (at 4 months and 1 year, relative to baseline)

Quantitative Coronary Angiography of the treated chronic total occlusions:

- in-stent and in-segment late luminal loss at 12 months

- in-stent and in-segment minimal luminal diameter

- in-stent and in-segment binary restenosis rate

Repeat Hospitalization for cardiac causes at 30 days, 4 months, and 1, 2, 3, 4, and 5 years

Presence of clinically overt heart failure at 30 days, 4 months, and 1, 2, 3, 4, and 5 years

Implantation of implantable cardioverter-defibrillator devices

Functional Class: NYHA classification at 30 days, 4 months, and 1, 2, 3, 4, and 5 years

*Excluding the initial percutaneous coronary intervention of the chronic total occlusion when randomly

assigned to this treatment arm. MRI: Magnetic resonance imaging NYHA: New York Heart Association

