### Post-STEMI Treatment for Patients with non CTO co-existing coronary lesions

In view of the weak guideline recommendations [14] and the different local practices, our protocol recommends a conservative approach for non-CTO co-existing lesions in the EXPLORE trial. In order to assess the value of CTO revascularization but in view of current daily clinical practice, the decision of the management of non-CTO co-existing lesions must be made before randomization. This decision is made by the local heart team, which generally consist of an interventional cardiologist and or a cardio-thoracic surgeon. In case it is decided that a non-CTO co-existing lesion should be treated, this additional PCI procedure must be performed within one week after the index STEMI. For patients randomized to recanalize the CTO, this additional PCI procedure will be performed during the same procedure as the CTO lesion is being treated. For patients in the conservative group, this additional PCI for non-CTO co-existing lesions will be scheduled within one week after the index STEMI. After the first week, revascularization is only indicated when clinically and or ischemia driven and is preferably performed after four months.

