### Safety and Other Secondary Endpoints

Safety will be determined by the assessment of Major Adverse Coronary Events (MACE) defined as cardiac death, peri-procedural myocardial infarction, myocardial infarction or any repeat coronary intervention at 30 days, 4 months and 1, 2, 3, 4, 5 years. Furthermore, safety is also determined by the occurrence of stent thrombosis. All safety endpoints are defined in accordance with the ARC [15]. The trial will be monitored by a Data and Safety Monitoring Board (DSMB) and the trial will be discontinued in case of safety concerns.

All other secondary endpoints are displayed in Appendix C.

A pre-specified subgroup analysis will be performed in which the primary outcome, Major Adverse Coronary Events (MACE) and suitable other secondary endpoints will be stratified according to the presence of non-CTO co-existing lesions.

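### MACE exempts only the assigned CTO procedure, so non-CTO PCI planned before randomization is likely to count as an event in the conservative arm alone

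*Protocol article*

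**What the plan says.** Appendix C, Safety Endpoints, gives MACE as "Major Adverse Cardiac Events, defined as cardiac death, myocardial infarction or any repeat coronary" intervention, from 30 days to 5 years. A footnote to that list is the only exemption: "Excluding the initial percutaneous coronary intervention of the chronic total occlusion when randomly" assigned to the CTO arm.

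The main text (Safety and Other Secondary Endpoints) gives the composite as "defined as cardiac death, peri-procedural myocardial infarction, myocardial infarction or any repeat coronary intervention" and states no exemption. It refers to the ARC for the safety definitions and plans a subgroup analysis of MACE by presence of non-CTO co-existing lesions.

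The section on post-STEMI treatment of non-CTO lesions requires that "the decision of the management of non-CTO co-existing lesions must be made before randomization". Where treatment is chosen, it depends on the arm as follows:
- CTO arm: "this additional PCI procedure will be performed during the same procedure as the CTO lesion is being treated".
- Conservative arm: "For patients in the conservative group, this additional PCI for non-CTO co-existing lesions will be scheduled within one week after the index STEMI".

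Neither MACE definition mentions this planned non-CTO PCI.

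**The concern.** An endpoint should count the same thing in both arms. Here a treatment fixed before randomization, and so expected equally often in both arms, is delivered in two ways. In the CTO arm it is part of the procedure that the footnote exempts. In the conservative arm it is a procedure of its own in the first week, inside every MACE window, and no exemption covers it.

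If the events are counted that way, part of any MACE excess in the conservative arm comes from the counting rule and not from the treatment. The error always runs in favour of CTO PCI, on an endpoint meant to show whether CTO PCI is safe. It falls wholly on patients with non-CTO lesions, so the pre-specified subgroup split by those lesions carries it in concentrated form.

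**Working it through.** **Plan's own figure.** The article gives no MACE rate, event count or power for MACE, so there is nothing to reproduce.

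**Readings of the footnote for planned non-CTO PCI**

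| Reading | CTO arm | Conservative arm | Result |
|---|---|---|---|
| Natural: the combined procedure is the exempt one | not counted | counted | bias towards CTO PCI |
| Strict: only the PCI of the CTO itself is exempt | counted | counted | dilution |
| By purpose: planned treatment is never an event | not counted | not counted | no distortion |

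The third reading has no wording behind it. The footnote had to exempt the planned CTO PCI by name, which suggests that a planned PCI after the primary PCI would otherwise count as a repeat intervention.

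**Inputs**
- From Statistical Considerations: 150 patients per arm; two-sided p-values; Fisher's exact test for binary endpoints, taken here at the 5% level.
- Assumed, because the article does not give them: true MACE risk m, equal in both arms (10%, with 5% and 15% as alternatives); share q of patients with planned non-CTO PCI (2, 5 and 10%), independent of other MACE.

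**Natural reading.** Counted CTO-arm risk = m. Counted conservative-arm risk = 1 − (1 − m)(1 − q). The spurious difference is therefore q(1 − m).

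With m = 10%:
- q = 2%: 1 − 0.90 × 0.98 = 11.8%, a difference of 1.8 points
- q = 5%: 1 − 0.90 × 0.95 = 14.5%, a difference of 4.5 points
- q = 10%: 1 − 0.90 × 0.90 = 19.0%, a difference of 9.0 points

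The probability of p ≤ 0.05 is the sum of the exact binomial probabilities over all pairs of event counts that Fisher's test rejects:

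| True MACE | q = 0 | q = 2% | q = 5% | q = 10% |
|---|---|---|---|---|
| 5% | 2.4% | 6.5% | 27.3% | 76.0% |
| 10% | 3.3% | 5.6% | 17.6% | 54.4% |
| 15% | 3.4% | 4.9% | 12.8% | 40.7% |

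**Masking of harm (natural reading).** Assume true MACE of 15% with CTO PCI and 5% without, a difference of 10 points.
- q = 5%: counted conservative risk is 1 − 0.95 × 0.95 = 9.75%, so 5.25 points remain, and the chance of a significant result falls from 80% to 23%.
- q = 10%: counted conservative risk is 1 − 0.95 × 0.90 = 14.5%, so 0.5 points remain, and the chance is 4%.

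**Strict reading.** Both risks are inflated, and the true difference d shrinks to d(1 − q). In the same example 10 points become 9.5 at q = 5% and 9.0 at q = 10%. With no true difference, none is created.

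**Subgroup.** If a share s of patients has non-CTO lesions, the share with planned non-CTO PCI within that subgroup is q/s. With s assumed to be 50%, q = 5% overall becomes 10% in the subgroup. At m = 10% the spurious difference there is 9.0 points instead of 4.5, and it is zero in patients without such lesions.

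**The case against.** The strongest reply is that the bias needs the footnote to be read broadly in one arm and strictly in the other. The footnote names only PCI of the CTO. Taken literally, a non-CTO lesion treated in the same session is not exempt in the CTO arm either, and the result is dilution, not bias. This stands as a limit: the text does not settle the matter, and a reader who infers that the bias is certain goes too far. It does not remove the problem, because a combined procedure is most naturally handled as one procedure and neither definition says how to split it.

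Second, the article condenses a fuller protocol, cites the ARC, and has an events committee adjudicate all MACE. The handling of staged procedures may be settled there. That is possible, but the exemption is stated here, and it is stated for one arm's procedure only.

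Third, the sizes are assumed. The article recommends a conservative approach to non-CTO lesions, which points to a small share, and at 2% the false-positive rate is only about 6%. The article also assigns significance for clinical outcomes such as MACE to a Cox model, so the Fisher probabilities are an illustration. Early events counted in one arm only would bias the Cox model in the same direction. All of this stands.

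Fourth, harm would not be invisible. Stent thrombosis is a separate safety endpoint, deaths, re-infarction and repeat PCI are collected individually, and the safety board reviews more than the composite. This also stands.

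Two further criticisms are tempting and should not be made:
- A reader might infer that a later first CTO PCI in a conservative patient is a crossover wrongly counted as an event. The article bars CTO intervention in that arm only for the first four months. A later procedure is a legitimate outcome of the conservative strategy.
- A reader might infer that the two MACE definitions contradict each other on peri-procedural MI. It is a kind of MI, and Appendix C does not exclude it, so the difference is one of wording.

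**Conclusion.** The concern holds at moderate severity. As written, the counting rule does not treat planned non-CTO PCI symmetrically on its natural reading, and the direction of the error favours CTO PCI. On the strictest reading the cost is dilution. The main text states no exemption at all, so the two definitions also differ on which procedures count.

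The size cannot be determined from the article. With true MACE assumed at 10% in both arms, the false-positive rate rises from about 3% to about 6, 18 and 54% for shares of 2, 5 and 10%. These figures assume the natural reading, independence of planned PCI from other events, and Fisher's test.

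A reader might infer that the trial's main result is at risk. It is not: MACE is secondary, and LVEF and LVEDV at four months do not depend on this rule. What is exposed is the MACE comparison and, most of all, its subgroup analysis by non-CTO lesions.

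**What to change.** Use one MACE definition, worded identically in the main text and in Appendix C. In its repeat-intervention component exclude, in both arms, PCI of a non-CTO lesion that was recorded before randomization as planned and was done within the first week. Keep the existing exemption for the assigned initial CTO PCI. Have the events committee adjudicate against the pre-randomization record.

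With this rule the spurious difference is zero, and Fisher's false-positive rate at 150 per arm returns to 2.4, 3.3 and 3.4% for true MACE of 5, 10 and 15%.

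The cost is small: one recorded field for a decision that must already be made before randomization, and slightly fewer counted events. The change concerns event counting only and leaves patient care as it is.
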